#### Aim 2 Analysis

To estimate the long-term effects of the intervention, we will again use linear mixed effects models. Fixed effect terms in the models include the group variable to represent the treatment effect and baseline outcome measurement. Participant-specific random effect terms will be used to account for within-participant correlation in repeat measures.

#### Aim 3 Analysis

We will construct machine learning models, in particular, random forest models, to predict outcomes based on patient group assigned, patient’s personal characteristics (eg, self-efficacy, sex, education, family income, and computer experience), and environmental factors (eg, distance from care and quality of internet connection). A random forest model consists of a large ensemble of regression trees and the average prediction of these trees will be output as the prediction of the model. Regression trees can accommodate nonlinearity and complex interaction without manual specification by researchers, but have the disadvantage of noisiness. Random forest retains the advantage of tree, while reducing noise by introducing randomness in the form of training each component tree with a bootstrap sample of the original training data and randomly selecting a subset of predictors as candidate for splitting at each split of the tree, to reduce the correlation between the trees and the variance of average prediction. We will use a random 70/30 partition (stratified by group and baseline pain) to reserve 30% of the patient sample as the test set, with the remaining 70% as the training set. We will use cross validation to optimize the parameters (minimal node size and number of random features selected for each split) for the random forest prediction models. The models, trained and optimized on the training data set, will be assessed using the reserved test data set to obtain an unbiased estimate of its performance when applied to new data. These models will allow us to identify individuals most likely to benefit from the proposed intervention and the modifiable environmental factors to improve the effects of the intervention.

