### Sample Size

For those who meet the eligibility criteria, we anticipate enrolling 195 participants to retain 170 (87.2%) participants with complete data at 8 weeks, based on a 13% attrition rate observed in our previous longitudinal studies in which follow-up was more than a year. We will strive for a sample in which 95% participants have African descent and approximately 50% are women. Our team has been exceptionally successful in conducting longitudinal studies using tablet technology with this vulnerable population and recruiting and retaining patients with SCD for pain research [16,47-50].

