### Statistical Analysis

#### Overview

The study biostatistician will perform data management and analysis in collaboration with the PI and coinvestigators. The data will be stored in an SQL database and exported to the statistical software R for analysis. We will use an intention-to-treat approach, which includes all randomized participants in our analysis. We will consider *P*<.025 as statistically significant for intervention efficacy tests (short term and long term) on the primary outcome of pain intensity. For other inferences, we will consider *P*<.05 to be statistically significant. We will compute descriptive statistics (frequencies, means, SDs, etc) of baseline patient characteristics data, including demographics, pain, stress, and analgesic use before the test and compare the control group and the experimental group using chi-square tests or 2-tailed *t* tests. We expect no significant difference between the 2 randomly generated groups.

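### Aim 3 judges its random forests on one 30% hold-out of about 51 to 59 patients: a valid estimate, but an imprecise and inefficient use of the sample

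*Protocol article*

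**What the plan says.** The Aim 3 Analysis section of the protocol article commits to one split: "We will use a random 70/30 partition (stratified by group and baseline pain) to reserve 30% of the patient sample as the test set". Cross-validation appears there only as the tool for tuning node size and the number of candidate features per split. Performance is measured once: "The models, trained and optimized on the training data set, will be assessed using the reserved test data set to obtain an unbiased estimate". The section then gives the models a practical use: "These models will allow us to identify individuals most likely to benefit from the proposed intervention and the modifiable environmental factors". It names no performance metric, no interval and no precision target.

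Two passages bear on how many patients enter the split. Sample Size states: "we anticipate enrolling 195 participants to retain 170 (87.2%) participants with complete data at 8 weeks, based on a 13% attrition rate". The Overview of the Statistical Analysis section states: "We will use an intention-to-treat approach, which includes all randomized participants in our analysis". The base is therefore 170 or, if every randomised patient contributes to Aim 3, up to 195.

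**The concern.** A single hold-out of this size gives a performance figure that depends a good deal on which patients happen to fall into it. The reserved 30% never help to build the model, and the other 70% never help to judge it. The plan already runs cross-validation for tuning, so the machinery that would let every patient serve both purposes is at hand but is not used for the assessment.

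Aim 3 is one of the three stated aims and includes evaluating the models. The hold-out result is the only performance figure the section promises. If it is noisy, a moderately predictive model may look close to useless, or a weak one may look good, through the luck of one partition. The issue is precision and efficiency, not bias. It is also separate from whether a model that predicts outcome can show who benefits.

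**Working it through.** **Inputs from the article.** Split 70/30, one partition (Aim 3 Analysis); 195 enrolled and 170 retained (Sample Size); all randomised participants analysed (Overview); SD of pain 3 (Sample Power).

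**Inputs assumed.** Number of predictors (8 or 10), how predictable the outcome is, and the shape of the data. The documents give none of these. Eight is the count of the predictors named as examples in Aim 3 (five personal and two environmental) plus group.

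**Step 1: base and split.** The plan's own retention figure reproduces: 170/195 = 87.2%. The article states no test-set size, so it follows from the split:
- N = 170: test 0.3 × 170 = 51 (about 25 per arm), training 119.
- N = 195: test 0.3 × 195 = 58.5 (about 29 per arm), training about 136.

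**Step 2: analytic precision of a hold-out.** Take R-squared as the squared correlation r between predicted and observed values. The 95% interval is tanh(atanh r ± 1.96/√(n − 3)), squared. For R-squared 0.2 and n = 51: r = 0.447, atanh r = 0.481, 1.96/√48 = 0.283. The limits for r are 0.20 and 0.64, so R-squared runs from **0.04 to 0.41**. With n = 59 it runs from 0.05 to 0.40. At other assumed values with n = 51, R-squared 0.1 gives 0.00 to 0.30, 0.3 gives 0.10 to 0.51, and 0.5 gives 0.29 to 0.68.

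For the RMSE of prediction, the limits are the estimate times √(n/χ²) at the 97.5% and 2.5% points of chi-square on n degrees of freedom. With n = 51 the factors are 0.838 and 1.240, or −16% to +24%. With n = 59 they are −15% to +22%.

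**Step 3: single split against cross-validation on the same patients (simulation).** The ranges are the central 95% of the estimated R-squared. The spread is the SD over simulated trials, except in the first row, where it is the root mean square error against the model's true R-squared.

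| Assumed setting | Single 70/30 split | Cross-validation, all patients | Variance ratio |
|---|---|---|---|
| Forest, N = 170, 10 predictors, predictable share 0.4 | −0.02 to 0.41; 0.099 | 0.14 to 0.37; 0.061 | (0.099/0.061)² = 2.6 |
| Forest, N = 170, 8 predictors, share 0.4 | 0.01 to 0.35; 0.086 | 0.13 to 0.34; 0.058 | (0.086/0.058)² = 2.2 |
| Forest, N = 195, 8 predictors, share 0.4 | 0.09 to 0.38; 0.075 | 0.15 to 0.35; 0.052 | (0.075/0.052)² = 2.1 |
| Linear learner, N = 170, 8 predictors, share 0.2 | −0.15 to 0.35; 0.125 | 0.04 to 0.27; 0.060 | (0.125/0.060)² = 4.3 |

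The widths for the single split are 0.43, 0.34, 0.29 and 0.50. The forest rows use about 90 to 120 simulated trials each, with fixed settings (minimum leaf 5) and no tuning.

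**Step 4: the same comparison with tuning nested inside the folds.** With a ridge learner, 10 predictors, N = 170 and predictable share 0.1 to 0.4, the error of the hold-out R-squared was 0.09 to 0.125. For repeated nested cross-validation it was 0.046 to 0.068. If the lower ends belong together and the upper ends likewise, the variance ratios are (0.09/0.046)² = 3.8 and (0.125/0.068)² = 3.4.

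**Step 5: gain in the model itself.** The forest's true R-squared on new patients, trained on 70% and then on all, was 0.254 and 0.275 (first row), 0.224 and 0.243 (second row), and 0.230 and 0.248 (third row). The gain is about 0.02 each time.

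**The case against.** The strongest reply is that nothing in the section is wrong. A stratified hold-out, split by patient and kept out of tuning, is a standard and valid method, and the claim of an unbiased estimate is fair for the model trained on the 70%. That stands. The point is only that another valid method gets more from the same patients.

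Several stronger readings are tempting, and the documents do not support them:

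- *The performance figure is too imprecise to use, so the evaluation in Aim 3 goes unanswered.* The article sets no metric or precision target against which to fail it. A wide unbiased estimate is still an evaluation, and RMSE would be known to within roughly −16% to +24%. Cross-validation also leaves real uncertainty (0.13 to 0.34 in the second row). Much of the limit is the sample size, not the split.
- *The trained model is materially weaker.* The loss is about 0.02 in R-squared. Refitting on all patients is not ruled out, and a condensed article may leave that detail to a fuller document, so its absence is no fault.
- *The split is why the models cannot show who benefits.* With SD 3, a contrast of treatment effect between two equal halves of 51 patients has a half-width of 1.96 × 2 × 3 × √(4/51) = 3.3 points. With all 170 it is still 1.8 points, against a design effect of 1.5. Changing the split does not settle that question.

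Two technical objections have some force. The forest simulations used fixed settings, so they do not test the tuned procedure. The nested check in Step 4 largely answers this, though with a ridge learner and not a forest. And an interval around a cross-validated R-squared is harder to obtain than one around a hold-out, because the out-of-fold predictions share training data.

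**Conclusion.** The point holds as one of precision and efficiency. The article fixes one random 30% hold-out of about 51 patients (about 59 on the full 195) as the sole basis for judging the Aim 3 models. In the assumed settings, the hold-out R-squared has a central 95% range roughly 0.3 to 0.5 wide, and cross-validation over all patients reduces the error variance by a factor of about 2 to 4. Using 195 in place of 170 does not change the conclusion.

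These sizes depend on assumed predictors and predictability. The direction was the same in every setting tried. The hold-out is not biased for the model it assesses, and the efficacy analyses of Aims 1 and 2 do not depend on it. This is a cheap improvement, not an error that threatens the trial.

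**What to change.** In the Aim 3 Analysis section, replace the single 70/30 partition with repeated nested cross-validation over all analysed patients (for example 10-fold, repeated):

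- Form folds by patient, stratified by group and baseline pain as the present split is.
- Tune node size and number of features inside each training fold, and do any imputation there too.
- Report out-of-fold R-squared and RMSE with an interval, for example by bootstrapping the whole procedure with copies of a patient kept in the same fold.
- State the number of patients used, and fit the final model on all of them.

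The cost is a change of wording and more computing time. No new patients, visits or data are needed. There would no longer be one untouched test set, although no patient is predicted by a model trained or tuned on that patient. The interval is also less simple than for a hold-out.

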### Study Aims and Hypotheses

The focus of this study is to evaluate the effectiveness of a self-management intervention that promotes the use of relaxation and distraction exercises (RDEs) in reducing pain, stress, and opioid dependency among adult outpatients with SCD. Specifically, the aims of this study are the following:

Determine the *short-term* effects of You Cope, We Support (YCWS). Hypothesis: In the first 8 weeks, compared with the control group, the experimental group will report reductions in the primary outcome—pain intensity (0-10 scale) and in the secondary outcomes—stress intensity (0-10 scale) and opioid use (OME).Determine the *long-term* effects of YCWS. Hypothesis: During months 3 to 6, compared with the control group, the experimental group will report reductions in the primary outcome—pain intensity (0-10 scale) and in the secondary outcomes—stress intensity (0-10 scale) and opioid use (OME).Use machine learning to develop and evaluate models that predict patient outcomes based on their group assignment and their personal (eg, self-efficacy, sex, education, family income, and computer experience) and environmental characteristics (eg, distance from care and quality of internet connection). The results will provide insight into the heterogeneity of intervention’s effects and the patients most likely to benefit from YCWS.

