#### Sample Power

The success of this study lies on its short-term and long-term efficacy on the primary outcome of pain intensity. We conservatively assume an SD of 3 for pain intensity based on values we observed in earlier studies. With a 2-sided type I error of 0.025, the proposed sample of 170 patients provides 80% power to detect a pain reduction of 1.5, below the minimal pain reduction of 2, which is considered as clinically meaningful.

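### Aim 3 trains and tests random forests on outcome prediction only, which as described does not support the conclusion that the models identify who benefits from YCWS

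*Protocol article*

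**What the plan says.** Under Study Aims and Hypotheses, the third aim is to build machine learning models of patient outcomes. Their results are meant to give insight into how the intervention's effect varies and into "the patients most likely to benefit from YCWS".

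The Aim 3 Analysis section sets out the method. Random forests are built "to predict outcomes based on patient group assigned", together with personal characteristics such as self-efficacy, sex and education, and environmental ones such as distance from care and internet quality. On validation it says: "We will use a random 70/30 partition (stratified by group and baseline pain) to reserve 30% of the patient sample as the test set". Node size and the number of features tried per split are tuned by cross-validation. The tuned models are then assessed on the reserved patients "to obtain an unbiased estimate of its performance when applied to new data". The section ends with the conclusion "These models will allow us to identify individuals most likely to benefit from the proposed intervention", and adds that the models will also show which modifiable environmental factors could improve the intervention's effects.

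The article does not define an individual benefit. It also describes no comparison of predicted benefit with an observed difference between arms.

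**The concern.** Whether a patient benefits depends on the difference between two outcomes, one under YCWS and one under control. The plan's only performance check asks how close the predicted outcome is to the observed outcome. A forest can do well on that check because baseline pain, self-efficacy or income predict later pain in both arms alike, while the treatment effect is the same for everyone. The hold-out result would look much the same in either case.

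At stake is a responder profile that the trial's own validation can neither confirm nor refute. The sentence on modifiable environmental factors has a related problem. Those factors are observed, not randomised, so a statement that changing them would improve the effect is causal and goes beyond the design.

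**Working it through.** **The plan's own figures.** Aim 3 states no sample-size or precision figure. The only power statement, under Sample Power, concerns the main effect on pain: 170 patients, SD 3, difference 1.5, two-sided alpha 0.025, 80% power. Recomputed with 85 per arm:
- SE = 3 × √(2/85) = 0.460
- 1.5/0.460 − 2.241 = 1.02, which gives power of about 84.6%.

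The stated 80% is therefore conservative. It has no bearing on Aim 3, but it supplies the SD and the size of effect the trial is built to detect.

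**Size of the hold-out.** The test set is 0.30 × 170 = 51 patients, about 25 or 26 per arm, with 119 for training. If all 195 patients to be randomised are used, it is 0.30 × 195 = 58.5, so 58 or 59, about 29 per arm.

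**Precision if benefit were checked directly.** Split the patients into predicted high-benefit and low-benefit halves, and compare the between-arm difference in the two halves. This uses four cell means of n/4 patients each, so SE = SD × √(4/(n/4)) = 4 × SD/√n.

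| Patients used | SD | SE | 95% half-width (1.96 × SE) |
|---|---|---|---|
| 51 (30% of 170) | 3 | 12/√51 = 1.68 | 3.3 |
| 58 (30% of 195) | 3 | 12/√58 = 1.58 | 3.1 |
| 170, out-of-fold | 3 | 12/√170 = 0.92 | 1.8 |
| 195, out-of-fold | 3 | 12/√195 = 0.86 | 1.7 |
| 51 | 2 (assumed) | 8/√51 = 1.12 | 2.2 |
| 170, out-of-fold | 2 (assumed) | 8/√170 = 0.61 | 1.2 |

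At SD 3 and two-sided alpha 0.05, the difference in effect detectable with 80% power is (1.96 + 0.84) × SE. That is about 4.7 points with 51 patients and 2.6 with 170 (4.4 and 2.4 if 195 are randomised). Power for a 1.5-point difference in effect is about 14% with 51 and 37% with 170 (16% and 42% if 195 are randomised).

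**Does hold-out performance respond to heterogeneity?** A small simulation used 60 trials per scenario, each with 170 patients split 119/51, and a forest of 100 trees on group plus nine covariates. The assumptions were a baseline-outcome correlation of about 0.6 and a mean effect of 1.5. Tuning values were fixed and the split was not stratified, so this illustrates the principle and does not forecast this trial.

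| True variation in effect | Mean hold-out R² | Predicted benefit gap, high vs low half | True gap |
|---|---|---|---|
| none | 0.23 | 0.42 | 0 |
| ±0.75 | 0.25 | 0.46 | 0.35 |
| ±1.5 | 0.25 | 0.52 | 1.38 |

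R² hardly moves between a uniform effect and one that varies widely. With no heterogeneity at all, the forest still predicts a benefit gap of 0.42 points.

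**The case against.** A reader might infer that this forest can say nothing about benefit, that the 70/30 split is invalid, or that only a causal forest or R-learner would do. The documents do not support any of these.

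- Randomised group is a predictor, and trees were chosen because they can capture interactions. Predicting each patient under both assignments and taking the difference gives a usable benefit score. In the simulation, that score correlated about 0.5 with true benefit when effects varied by ±1.5.
- It might also be said that the forest will neglect group because features are offered at random. But the number of features per split is tuned, so group may be offered often.
- A stratified hold-out, with tuning kept to the training data, is a valid way to estimate outcome-prediction performance. That is all the plan claims for it.
- The choice of learner is a preference among several acceptable methods.

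The half-widths above also price a check the article does not plan, at an SD the protocol itself calls conservative. If predictors explained 36% of the variance (an assumption), 3.3 would become 3.3 × √0.64 = 2.6. Aim 3 carries no hypothesis, and the aims promise only insight.

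Finally, the full protocol or analysis plan is not shown and may define a benefit score. Its absence from a condensed article would not be a finding. What stands is what the article asserts: it places a conclusion about benefit directly after a check of outcome prediction. Nothing elsewhere in the article limits that conclusion or the one on environmental factors.

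**Conclusion.** The point holds for the analysis as described. Hold-out accuracy in predicting outcomes is not evidence about who benefits, so the closing conclusion of the Aim 3 Analysis section does not follow from the assessment before it. The clause on modifiable environmental factors needs the same restraint.

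Checking predicted benefit on the hold-out alone would leave a 95% half-width of about 3.1 to 3.3 points at SD 3, roughly twice the 1.5-point main effect the trial is sized for. Using all patients gives about 1.7 to 1.8. At an assumed SD of 2 with 170 patients, the figures are about 2.2 and 1.2. They rest on a normal approximation with equal cells and treat out-of-fold groups as fixed, so they are approximate. Even the better analysis may not detect heterogeneity.

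This should be changed, but it is not critical: the efficacy analyses in Aims 1 and 2 are unaffected.

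**What to change.** - Define predicted benefit as each patient's predicted outcome under YCWS minus that under control, from the planned forest or from a learner that targets the treatment effect directly.
- Obtain it out-of-fold by cross-fitting over all randomised patients, so that no patient's score comes from a model trained on that patient.
- Report the observed between-arm difference with its confidence interval by predicted-benefit group, labelled exploratory.
- Keep the outcome forest and its 30% hold-out, described as prognostic only.
- Describe environmental factors as associations or effect modifiers, not as causes of a better effect.

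If the benefit analysis is not wanted, the alternative is to limit the Aim 3 conclusion to outcome prediction. No new data are needed. The cost is some extra computing, revised wording and a more modest conclusion, which may be that heterogeneity cannot be established at this sample size.

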#### Missing Data

Random effect models can accommodate longitudinal data with missing visits. For visits with partial data (item-level missing data), we will use multiple imputation by fully conditional specification to generate multiple completed data sets, on each of which statistical inference will be performed separately and then aggregated using Rubin rule [72]. This allows us to fully use the information provided by the participants.

#### Sample Power

The success of this study lies on its short-term and long-term efficacy on the primary outcome of pain intensity. We conservatively assume an SD of 3 for pain intensity based on values we observed in earlier studies. With a 2-sided type I error of 0.025, the proposed sample of 170 patients provides 80% power to detect a pain reduction of 1.5, below the minimal pain reduction of 2, which is considered as clinically meaningful.

## Results

The project was funded by the National Institutes of Health and National Institute of Nursing Research. Our IRB approved the study on May 14, 2020.

Study recruitment started on March 29, 2021. As of April 2022, we had enrolled 45.9% (78/170) participants in the study. Of the 78 participants, 65 (83%) participants have completed baseline, 53 (68%) have completed the postintervention assessment after 8 weeks, and 28 (36%) have completed the 6-month study.

